### Outcome measures

2.12

#### Primary outcome measure

2.12.1

##### Changes in protrusion size

2.12.1.1

MR images were assessed to measure changes in protrusion size. A 1.5-T MRI system (Siemens, Erlangen, Germany) was used with a spin-echo sequence. Eleven sections were scanned on T1- and T2-weighted sagittal views with an interlamellar spacing of 1.25 mm and a section thickness of 5 mm. The image data were scanned and processed by Picture Archiving and Communication Systems. The volume and resorption rate of the protrusion were calculated according to the method described by Autio.^[18]^ MRI scans were performed on the first visit, the second visit, and the final follow-up to calculate the volume of the protrusion (ie, baseline and 3- and 6-month follow-up). T2-weighted sagittal view MR image showing how the resorption rate is calculated.^[16]^ The internal boundary of the protrusion is the line connecting the posterior inferior margin of the upper centrum and the posterior superior margin of the lower centrum. The external boundary is the protrusion edge. A proficient MRI operator can determine the area of the protrusion, as shown in the right panel. The volume of the protrusion (mm^3^) = (inter-section spacing + section thickness) (mm) ×Σ area of the protrusion in each section (mm^2^). The resorption rate = (volume of protrusion before treatment—volume of protrusion after treatment/volume of protrusion before treatment) ×100(%). Representative images are shown in Figure 2.

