**Methods::**

The present study design is for a single-center, 2-arm, open-label randomized controlled trial. A total of 150 eligible LDH patients will be randomly assigned to either a TCM treatment group or a control group in a 1:1 ratio. Patients in the TCM group will be administered a TCM decoction for 4 weeks. Patients in the conventional drug control group will be instructed to take a specific daily dose of celecoxib. The primary outcome measure is the change from baseline in the volume of the protrusion, as assessed using MR images. Secondary outcome measures include visual analog scale pain scores and Japanese Orthopaedic Association scores assessed at 3 and 6 months.

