### Blinding

2.7

Because the study will be an open-label clinical trial, both patients and clinicians will know which treatment is being administered, and patients are required to cooperate with their physicians prior to treatment. The assessment of clinical efficacy will be carried out by telephone by a clinical assessor who will be masked to the treatment assignment. During the data collection and analysis stages, the clinical researchers, assessors, and statisticians will not share study information.

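### Section 2.7 masks only the telephone assessor; no stated masking covers the operator who measures the primary MRI outcome

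*Protocol article*

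**What the plan says.** The abstract fixes the endpoint: "The primary outcome measure is the change from baseline in the volume of the protrusion, as assessed using MR images". Section 2.12.1 agrees. (Section 2.13.1 gives the VAS the same rank, which is a separate inconsistency; this point follows the abstract and 2.12.1.)

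Section 2.7 sets out who knows what:

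- "Because the study will be an open-label clinical trial, both patients and clinicians will know which treatment is being administered".
- "The assessment of clinical efficacy will be carried out by telephone by a clinical assessor who will be masked to the treatment assignment".
- During data collection and analysis, "the clinical researchers, assessors, and statisticians will not share study information".

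Section 2.12.1.1 describes the MRI measurement in some detail: field strength, sequence, number of sections, spacing, boundaries and volume formula. The inner boundary is a line between bony landmarks. For the outer one the text says only: "The external boundary is the protrusion edge". On who measures, it says: "A proficient MRI operator can determine the area of the protrusion". It does not say whether that operator is masked to arm or to visit.

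**The concern.** The only assessment to which section 2.7 attaches masking is done over the telephone, and an MRI area cannot be measured that way. Followed as written, the plan therefore leaves its primary outcome without stated masking, in a trial where patients and clinicians know the treatment.

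This matters more here than for the pain score. The VAS is marked by patients who know their arm, so masking an assessor protects it only in part. An MR image with its labels removed says little about treatment, so the MRI reading is the outcome that masking could protect best. If the operator knows the arm, uncertainty about where the edge lies can be resolved differently in the two groups, and the between-group comparison absorbs the difference.

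**Working it through.** The plan states no figure on this point, so there is nothing to reproduce. The check has a textual part and an illustrative part.

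**1. Roles against outcomes**

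| Outcome | Who produces it | Masking stated |
|---|---|---|
| Clinical efficacy by telephone (2.7) | Clinical assessor | Yes, to treatment |
| Protrusion volume on MRI, primary (2.12.1.1) | MRI operator | None |

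**2. How a reading error reaches the endpoint**

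Section 2.12.1.1 gives V = (1.25 + 5) × Σ area = 6.25 × Σ area. V is linear in area, so if every area is read low by a fraction b, the measured volume is (1 − b)V. A proportional error in area is the same proportional error in volume.

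**3. Arm knowledge and visit knowledge act differently**

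Let μ_T and μ_C be the true mean follow-up volumes, with comparable baselines.

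- *Operator knows the arm and reads TCM follow-up scans low:* measured difference = (1 − b)μ_T − μ_C. With no true effect (μ_T = μ_C = μ) this is −bμ, a false difference between arms.
- *Operator knows the visit but not the arm:* measured difference = (1 − b)(μ_T − μ_C). With no true effect this is 0.
- *Within one arm, visit known:* measured reduction = V₀ − (1 − b)V₁ = (V₀ − V₁) + bV₁. With no true change the apparent resorption rate is b.

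The third case matters if the matched-data t-test that section 2.14 names for volume is applied within groups, baseline against follow-up.

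**4. Size, for illustration only**

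Assumed, not from the document: b = 5–10% between arms; SD of volume = 30–50% of its mean.

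- Lower end: 0.05 / 0.50 = 0.10 SD.
- Upper end: 0.10 / 0.30 = 0.33 SD.

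For scale, section 2.13.3 gives 75 per group, 15% dropout, α = 0.05 and power 0.90, but no effect size. Then 75 × 0.85 = 63.75, about 64 per group. The difference detectable in a two-sided test is (1.960 + 1.282) × √(2/64) = 0.573 SD (one-sided, 0.517; the article does not state which). The illustrative shift is 0.10/0.573 = 0.17 to 0.33/0.573 = 0.58 of that.

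False-positive rate of a two-sided z-test with no true effect, 64 per group, SE = √(2/64) = 0.177, shift s in SD units: 1 − Φ(1.96 − s/SE) + Φ(−1.96 − s/SE).

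| Assumed shift s | False-positive rate |
|---|---|
| 0 | 0.050 |
| 0.1 SD | 0.087 |
| 0.2 SD | 0.205 |
| 0.3 SD | 0.396 |

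**5. Limit of the scale**

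The endpoint is change, not volume. With equal SDs at both visits and correlation r between them, SD(change) = SD × √(2(1 − r)). This equals the SD of volume only at r = 0.5. It is smaller for higher r, which makes the standardised shift larger, and the reverse for lower r. The article gives neither r nor the SD.

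**The case against.** The strongest reply rests on the last sentence of section 2.7. It separates researchers, assessors and statisticians, and the plural assessors might include whoever reads the images. On that reading, allocation information is meant not to reach the operator. This stands in part: a reader should not infer that nothing at all restricts what the operator learns. But the sentence does not name the operator, and keeping staff from exchanging information does not take a patient's identity or a scan date off an image.

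A second reply is that this is a condensed article and that image handling belongs in the full protocol. That has force for procedural detail. It has less for masking itself, because the article has a section devoted to blinding, assigns masking there, and assigns it to an assessment other than the primary one.

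Several stronger readings are tempting and are not supported:

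- *That the operator knows the arm.* Section 2.7 says this of patients and clinicians. Nothing says the operator treats patients or sees the allocation.
- *That the protrusion is traced by hand.* The article says an operator can determine the area; software assistance is not excluded, and Figure 2 is not available here. Only the outer edge clearly calls for judgement.
- *That knowing the visit biases the treatment comparison.* By step 3 of the working, visit alone creates no false difference between arms.

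**Conclusion.** The point holds as a gap in the stated masking. Section 2.7 covers the telephone assessment of clinical efficacy, and no statement covers the operator whose area measurements make up the primary outcome. That conclusion rests on the text alone.

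Its size is unknown. The 0.10–0.33 SD range and the false-positive rates show what a modest differential could do if it occurred. They depend on an assumed 5–10% reading difference, an assumed SD of 30–50% of mean volume, and the SD of volume standing in for the SD of change. A reader might infer that the primary result will be biased by that amount; the document gives no evidence that any such difference will occur. The risk to the between-group comparison comes from knowledge of arm. Knowledge of visit alone is mainly a risk to within-group statements about resorption.

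**What to change.** Add to section 2.7, and repeat in section 2.12.1.1, that:

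- MR series are exported under a code, with patient identity, treatment arm and acquisition date removed;
- the existing MRI operator measures each patient's three scans in random order, masked to arm and visit;
- the volumes are locked before allocation is linked to them.

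If this is already the practice, the change is a matter of wording. Otherwise the scans, the schedule and the operator stay the same. The cost is coding and shuffling the files, and reading in batches rather than as each visit occurs.

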**Figure 2 F2:**
[figure not shown]
Representative MR image to calculate the resorption rate. MR = magnetic resonance.

### Secondary outcome measures

2.13

#### VAS pain score

2.13.1

The primary efficacy endpoint of the study will be the VAS, which is a pain score ranging from 0 mm (no pain) to 100 mm (worst pain ever experienced). Operationally, the VAS score is usually a horizontal line, 100 mm in length, anchored by word descriptors at each end. Patients mark the point on the line representing the current pain level. The VAS score is then determined by measuring in millimeters from the left-hand end of the line to the point that the patient marked.^[19]^ The VAS score will be measured during each assessment visit (at baseline and 3-and 6-month follow-up)

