### Data analysis

2.14

Statistical analysis will be performed using SPSS 16.0. Measured data such as JOA scores and the volume of the protrusion will be compared using Student *t-*test for matched data; whereas enumerated data, such as the improvement in the JOA score, will be compared using the chi-squared test or Fisher exact probability test. *P* <.05 will be considered significant for all statistical tests.

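### The protocol names two different primary endpoints, MRI protrusion volume and VAS pain, and does not say which visit carries the primary test

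*Protocol article*

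**What the plan says.** On the primary endpoint:

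- Abstract, Methods: "The primary outcome measure is the change from baseline in the volume of the protrusion, as assessed using MR images". The next sentence places VAS elsewhere: "Secondary outcome measures include visual analog scale pain scores and Japanese Orthopaedic Association scores assessed at 3 and 6 months".
- Section 2.12.1, headed as the primary outcome measure, contains only the MRI assessment (2.12.1.1): "MR images were assessed to measure changes in protrusion size".
- Section 2.13.1, under the heading for secondary outcome measures: "The primary efficacy endpoint of the study will be the VAS".

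On timing, section 2.12.1.1 has the MRI scans done "to calculate the volume of the protrusion (ie, baseline and 3- and 6-month follow-up"), and section 2.13.1 uses the same schedule for pain: "The VAS score will be measured during each assessment visit (at baseline and 3-and 6-month follow-up"). Neither visit is singled out for either outcome, and the abstract's statement of the primary outcome gives no time point.

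On error control, section 2.14 gives one rule. A P value below .05 "will be considered significant for all statistical tests".

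**The concern.** A trial needs one pre-stated answer to the question of which result decides it. Here the text gives two, and they differ in kind. One is a measurement read from images. The other is a patient-reported score in a trial that section 2.7 describes as open-label, where patients know their treatment and expectation can move the score. Which of the two carries the primary claim therefore affects how far the result can be trusted.

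If the conflict stays, a report that leads with volume and a report that leads with VAS could each cite the protocol in support. The unranked visits add a second choice of the same kind. A primary claim chosen after the data are seen does not have the 5% error rate that section 2.13.3 takes as its basis.

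**Working it through.** **Step 1. Which way does the text lean?**

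| Place | Points to |
|---|---|
| Abstract, Objective (resorption of the herniation) | volume |
| Abstract, Methods: primary outcome | volume |
| Abstract, Methods: VAS listed as secondary | volume |
| Heading 2.12.1 and its only content | volume |
| Heading 2.13, under which VAS sits | volume |
| Section 2.14: volume and JOA given as examples of measured data, VAS not named | volume |
| Section 2.13.1, opening sentence | VAS |

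Six cues favour volume and one explicit sentence favours VAS. The sample size section (2.13.3) does not settle it: it gives α = 0.05, power 0.90, 15% dropout and 150 participants, but names no endpoint or effect size. The figure of 150 therefore cannot be reproduced or tied to either outcome.

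**Step 2. What would be at stake if any nominal success counted?**

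Inputs from the document: two candidate endpoints, two visits, 0.05 for every test. Assumptions, because the document gives neither: success on any one test may be claimed as primary, and the test statistics are jointly normal with equal pairwise correlation r.

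If the k tests are independent, the chance of at least one false positive is 1 − 0.95^k:

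- two endpoints at two visits (k = 4): 1 − 0.95⁴ = 0.185
- one endpoint at two visits (k = 2): 1 − 0.95² = 0.0975

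For two-sided tests on jointly normal statistics, independence is the worst case (the Šidák inequality), so these are upper limits. Independence is implausible for the same measure in the same patients 3 months apart, so the correlated values are the more realistic ones:

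| r (assumed) | k = 4, two-sided | k = 4, favouring TCM | k = 2, two-sided | k = 2, favouring TCM |
|---|---|---|---|---|
| 0 | 18.5% | 9.6% | 9.75% | 4.9% |
| 0.5 | 15.6% | 7.8% | 9.1% | 4.5% |
| 0.7 | 13.0% | 6.5% | 8.4% | 4.2% |
| 0.9 | 9.4% | 4.7% | 7.0% | 3.5% |

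The columns favouring TCM count only errors in that direction. At r = 0 they are 1 − 0.975⁴ = 0.096 and 1 − 0.975² = 0.049. Their reference value is 2.5%, not 5%.

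**Step 3. Does correcting 2.13.1 alone suffice?**

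No. With VAS removed, volume at two unranked visits is the k = 2 case, which still gives 8.4% at r = 0.7 and up to 9.75%. With one endpoint at one visit, the rate is 5% and no adjustment is needed.

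**The case against.** The strongest reply is that the sentence in 2.13.1 is a slip. One sentence stands against the objective, the abstract and the headings, and changing one word removes the endpoint conflict. That is probably right, and it limits how much should be read into the sentence. It does not remove the contradiction: the sentence is explicit, and an analysis plan cannot make both statements true.

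A second reply is that the choice of visit and the handling of multiplicity are often left to an analysis plan, and that the P<.05 sentence is an ordinary nominal threshold which does not say that every test supports a primary claim. This is fair. The visit question is weaker than the contradiction and would not carry the point alone. It is included because correcting 2.13.1 without it leaves the primary test open.

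Three stronger readings are tempting and are not supported:

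- *The trial has a type I error of 18.5%.* That needs VAS to be genuinely co-primary, success on any one of four tests to suffice, and independence. The document states none of these. If success on all tests were required, the error rate would not inflate; power would fall instead.
- *Volume and resorption rate are rival primary scales.* Section 2.12.1.1 calculates both, but the abstract names change in volume and section 2.14 names volume as a quantity to be tested.
- *The resorption formula makes the outcome meaningless.* As printed, "The resorption rate = (volume of protrusion before treatment—volume of protrusion after treatment/volume of protrusion before treatment) ×100" divides only the second volume by baseline. This is a missing pair of brackets. The intended percentage reduction is plain, and the parallel JOA formula in 2.13.2 is bracketed correctly.

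**Conclusion.** The contradiction is real, and no other part of the document resolves it. It should be corrected before analysis because it concerns which result carries the trial's primary claim. The weight of the text favours change in protrusion volume.

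The error rates in the working are conditional. They show what the ambiguity could cost if any nominal success were claimed as primary. Under that assumption, a realistic figure is about 13–16% two-sided if both endpoints and both visits are in play, and about 8–9% if only the visit is open. Both ranges rest on assumed correlations of 0.7–0.5.

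**What to change.** 1. In section 2.13.1, describe VAS as a secondary endpoint, in line with the abstract and the headings of 2.12.1 and 2.13.
2. In section 2.12.1, name one visit in advance for the primary test of change in protrusion volume. Six months is one reasonable choice, but the document lists both visits equally and the decision is the sponsor's.
3. State that volume at the other visit, VAS, JOA and resorption rate are secondary and carry no primary claim.
4. As a minor editorial correction in 2.12.1.1, bracket the resorption rate as ((volume before − volume after) / volume before) × 100. A fall from 1000 to 600 mm³ then gives 40%.

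The cost is wording only. With one primary test at 0.05, no adjustment and no additional participants are needed. The downside is that VAS, or volume at the other visit, can no longer carry the primary claim.

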#### JOA score

2.13.2

The JOA score indicates the severity of clinical symptoms. The improvement in JOA score is calculated according to the following equation:^[16]^ Improvement according to JOA score (%) = (score after completion of treatment − score before treatment)/ (29 − score before treatment) × 100 (the maximum possible score is 29). An improved JOA score ≥75% was classified as excellent, 50% to 75% as good, 25% to 50% as fair, and <25% as poor. The JOA score will be measured during each assessment visit (ie, at baseline and 3- and 6-month follow-up).

#### Sample size calculation

2.13.3

The required sample size was calculated using G∗Power 3 software, developed by the Institute for Experimental Psychology (Heinrich-Heine University, Germany). For this trial, it was determined prospectively that α =0.05 and 1-β =0.90. Consistent with a previous trial on massage for LDH, a total of 150 participants will be included in this trial (75 in each group) to compensate for an anticipated dropout rate of 15%.

### Data analysis

2.14

Statistical analysis will be performed using SPSS 16.0. Measured data such as JOA scores and the volume of the protrusion will be compared using Student *t-*test for matched data; whereas enumerated data, such as the improvement in the JOA score, will be compared using the chi-squared test or Fisher exact probability test. *P* <.05 will be considered significant for all statistical tests.

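### The test stated for protrusion volume and JOA score is a matched t-test: it does not compare the arms, and a two-sample t-test in its place would still ignore the baseline value collected in every patient

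*Protocol article*

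**What the plan says.** The abstract defines the endpoint: "The primary outcome measure is the change from baseline in the volume of the protrusion, as assessed using MR images". Section 2.12.1.1 has volume measured three times: "MRI scans were performed on the first visit, the second visit, and the final follow-up to calculate the volume of the protrusion", that is at baseline, 3 months and 6 months. Section 2.13.2 does the same for JOA: "The JOA score will be measured during each assessment visit (ie, at baseline and 3- and 6-month follow-up"; section 2.13.1 gives the same schedule for VAS.

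Section 2.14 then states the analysis: "Measured data such as JOA scores and the volume of the protrusion will be compared using Student *t-*test". The sentence goes on to restrict this to the t-test for matched data, and adds a chi-squared or Fisher exact test for categorical data, with JOA improvement as the example. No covariate, regression model or other baseline adjustment is named. P below .05 "will be considered significant for all statistical tests".

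Section 2.13.3 gives the planning figures: "it was determined prospectively that α =0.05 and 1-β =0.90", and "a total of 150 participants will be included in this trial (75 in each group"), "to compensate for an anticipated dropout rate of 15"%. It states no effect size, SD, correlation or outcome behind the 90%. Section 2.6 describes 1:1 allocation from a random number generator and names no stratification.

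**The concern.** Two things are wrong with the stated test, one inside the other.

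First, a matched t-test asks whether volume changed within a set of patients. The Introduction reports resorption in 66.66% of herniations, so shrinkage is to be expected in both arms, and a significant within-arm change would say nothing about TCM against control.

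Second, the obvious repair, a two-sample t-test, is valid but wasteful. Under the definitions in the article, baseline could enter only by subtraction (change) or division (resorption rate, JOA improvement percentage). Subtraction fixes the baseline slope at 1. Division makes the outcome most variable in patients with a small protrusion, or with a JOA score near the maximum of 29. Neither lets the data set the slope.

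At stake is the precision of the primary comparison and its exposure to chance imbalance in starting volume, which nothing in section 2.6 is described as controlling.

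**Working it through.** **Inputs.** From section 2.13.3: alpha 0.05 (taken as two-sided; the article does not say), power 0.90, 75 per arm, 15% dropout. Assumed, because the documents are silent: equal variances at baseline and follow-up, and a baseline/follow-up correlation rho of 0.3 to 0.7.

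**The plan's own figure.** The 150 cannot be reproduced without an effect size. Solving backwards: 75 x 0.85 = 63.75, so about 63 evaluable per arm (63/0.85 = 74.1, rounded up to 75). The detectable standardised difference is (1.960 + 1.282) x sqrt(2/63) = 0.578. This shows only what a two-sample t-test with 90% power at that size would imply; it does not confirm that the plan assumed it.

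**Gain from ANCOVA.** Its residual variance, relative to a two-sample t-test, is
- 1 - rho^2 against follow-up values;
- (1 + rho)/2 against change scores.

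Power = Phi(3.242/sqrt(factor) - 1.960), where 3.242 = 1.960 + 1.282 corresponds to 90%.

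At rho = 0.5 both factors are 0.75: 3.242/sqrt(0.75) = 3.743, and Phi(1.783) = 96.3%.

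| rho | Factor vs change | Power | Gain | Factor vs follow-up | Power | Gain |
|---|---|---|---|---|---|---|
| 0.3 | 0.65 | 98.0% | +8.0 | 0.91 | 92.5% | +2.5 |
| 0.5 | 0.75 | 96.3% | +6.3 | 0.75 | 96.3% | +6.3 |
| 0.7 | 0.85 | 94.0% | +4.0 | 0.51 | 99.5% | +9.5 |

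At rho 0.5, ANCOVA would need 48 evaluable per arm for 90% power instead of 63. Against change scores the gain fades as rho rises (1.4 points at rho 0.9).

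**Chance imbalance.** The standard error of the baseline difference is sqrt(2/63) = 0.178 SD. An imbalance of that size shifts a follow-up comparison by rho x 0.178 and a change-score comparison by (1 - rho) x 0.178 in the opposite direction. At rho 0.5 both shifts are 0.089 SD, or 15% of 0.578. At rho 0.7 they are 0.125 SD for follow-up and 0.053 SD for change. A follow-up comparison favours the arm that started smaller; a change comparison favours the arm that started larger.

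**Choice of scale.** This was simulated with assumed log-normal volumes: medians 1000 and 600 mm3, log SD 0.5, arm effect -0.25 on the log scale, rho 0.5, 64 per arm. Power was about 35% for raw change, 75% for resorption rate, 85% for raw-scale ANCOVA and 90% for log-scale ANCOVA. An unadjusted t-test on log change already reached about 81%.

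The Introduction says lesions can resolve completely, so zero volumes must be expected. With an assumed 10% zeros in both arms, log ANCOVA with 1 added fell to about 10% power. Raw-scale ANCOVA kept 63%, against 57% for resorption rate and 27% for raw change.

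**The case against.** The strongest reply is that the matched test is the real fault, and that once it is corrected the covariate is a refinement. An unadjusted between-arm comparison of change is valid, and randomisation keeps it unbiased on average. That stands, and it limits the point to precision and to imbalance in the particular sample. It does not dispose of the point: an author told only to use an unpaired test would still leave baseline out, and ANCOVA settles both matters in one sentence.

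It can also be said that covariates are commonly left to a SAP, which is not shown here. That would answer silence. The article is not silent; it names a specific test that cannot carry a covariate.

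Four stronger readings are tempting, and the documents do not support them:
- A reader might infer that the plan demonstrably loses about 6 power points. That figure needs rho = 0.5 and a between-arm t-test with 90% power, and the article states neither.
- A reader might infer that the unadjusted result would be biased. It would not be, on average.
- A reader might take the simulated 35% against 90% as the value of adjustment. Most of that gap is scale: log change without a covariate already gives about 81%, and the data were generated to suit the log scale.
- A reader might say that the t-test is the only analysis of JOA. Section 2.14 also provides a chi-squared or Fisher test of JOA improvement, likewise unadjusted.

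**Conclusion.** The point holds as a cheap improvement the sponsor should make. As worded, the test for volume and JOA scores does not compare the arms, and its natural replacement would leave out a baseline value that every patient supplies.

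The size is conditional: about 4 to 8 power points against change scores, which is the stated primary outcome, and 2.5 to 9.5 against follow-up values. It rests on rho between 0.3 and 0.7, equal variances, two-sided alpha 0.05 and a 90% starting power that the article asserts but gives no means of checking. The case for the raw scale rests on the article's own remark about complete resolution; the 10% share of zeros used to illustrate it is an assumption.

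**What to change.** Reword section 2.14 as follows:
- Compare the arms by ANCOVA of follow-up protrusion volume on arm and baseline volume, and report the adjusted between-arm difference with its 95% CI.
- Fix the raw volume scale in advance. Do not use a logarithm with an added constant, and do not leave the scale to be chosen after seeing the data.
- Use the same model for JOA score and VAS.
- Keep the resorption rate, and the chi-squared or Fisher test of JOA improvement classes, as supporting analyses.

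The cost is one degree of freedom and a result expressed as an adjusted difference. No further patients, visits or scans are needed, and SPSS 16.0 fits the model.

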### Randomization

2.6

In this trial, participants will be randomly assigned to either the TCM group or the control group in a 1:1 ratio using a random number generator (SPSS 16.0, SPSS Inc, Chicago, IL).

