### Indications for surgery

2.11

Surgery will be indicated if:

(1)after the termination of all interventions, conservative treatment with the TCM regimen for 3 to 6 months has been ineffective (Japanese Orthopaedic Association scores <16); or(2)the patient experiences exacerbation or progression of radicular symptoms or cauda equina neurological signs at any stage during the treatment period.

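### The only test named for protrusion volume and JOA is a t-test, which gives up about 10 points of power against a baseline-adjusted repeated-measures model and, on raw 6-month values, can be biased if loss is selective and differs between arms

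*Protocol article*

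**What the plan says.** Section 2.14 (Data analysis) states "Measured data such as JOA scores and the volume of the protrusion will be compared using Student" t-test, and the sentence continues "test for matched data; whereas enumerated data, such as the improvement in the JOA score, will be compared using the chi-squared test or Fisher exact" test. No other method for volume or JOA as measured quantities appears in the article.

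The measurement schedule is richer than that test uses. On volume, section 2.12.1.1 says "MRI scans were performed on the first visit, the second visit, and the final follow-up to calculate the volume of the protrusion", and it identifies these visits as baseline, 3 months and 6 months. Section 2.13.2 gives the same three time points for JOA. The Abstract defines the primary outcome as the change in volume since baseline.

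Section 2.13.3 sets alpha and power ("it was determined prospectively that α =0.05 and 1-β =0.90") and says that "a total of 150 participants will be included in this trial (75 in each group) to compensate for an anticipated dropout rate of 15" per cent. It does not split the 15% by arm or by visit.

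The article does not say how missing values are handled or whether each visit is tested separately.

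**The concern.** A t-test takes one number per patient: a value at one visit, or one difference. Three things follow when an outcome has a baseline and two follow-up measurements.

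- A test on the 6-month value ignores baseline. A test on change uses baseline, but with a fixed coefficient of 1 instead of the best-fitting one. Both waste precision when the baseline correlation is moderate.
- If nothing is imputed, a patient without a 6-month value contributes nothing to the 6-month comparison, even when a 3-month scan exists. At 15% loss that is 0.15 × 150 = 22.5, so 22 or 23 patients.
- The unimputed comparison is safe only if loss is unrelated to the outcome, or related to it in the same way in both arms. In an open-label trial that cannot be taken for granted.

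At stake are some avoidable loss of power and, under particular loss patterns, a distorted 6-month contrast.

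**Working it through.** **The plan's own figure.** The total of 150 cannot be reproduced, because section 2.13.3 gives no effect size or SD. It is consistent with a two-sided standardised difference of 0.58: n = 2 × (1.960 + 1.282)² / 0.58² ≈ 62.5, so 63 per arm; 63 / 0.85 = 74.1, so 75 per arm and 150 in total. That 0.58 is back-solved, not stated.

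**Inputs.** From the article: 75 per arm, 15% loss, alpha 0.05 (taken as two-sided), visits at baseline, 3 and 6 months. Assumed: each visit has SD 1; correlations 0.6 (baseline to 3 months), 0.5 (baseline to 6 months) and 0.8 (3 to 6 months); true effect 0.5 SD.

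**Power under random loss.** Patients per arm with a 6-month value: 75 × 0.85 = 63.75. SE = √(2 × variance / 63.75), and power = Φ(0.5 / SE − 1.96).

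| Between-arm analysis | Variance | SE | Power |
|---|---|---|---|
| t-test, 6-month value | 1 | 0.177 | 81% |
| t-test, change | 2 − 2 × 0.5 = 1 | 0.177 | 81% |
| ANCOVA on baseline | 1 − 0.5² = 0.75 | 0.153 | 90% |

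For the repeated-measures model, given baseline:
- 3-month variance: 1 − 0.6² = 0.64
- 3-to-6-month covariance: 0.8 − 0.6 × 0.5 = 0.50
- part of the 6-month variance explained by the 3-month value: 0.50² / 0.64 = 0.391
- remainder: 0.75 − 0.391 = 0.359

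If 5% are lost before month 3, then 71.25 per arm have a 3-month value. SE = √[2 × (0.359 / 63.75 + 0.391 / 71.25)] = 0.149, and power is about 92%.

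These large-sample values agree with simulation, which gave about 80% for the t-tests, 90% for ANCOVA and 91% for the model. About 10 points separate the t-tests from the model, and all but 1 or 2 of them come from baseline adjustment. At an effect of 0.58 SD the same formulas give about 91%, 97% and 97%, so the gain shrinks as the true effect grows.

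**Bias under selective loss, no true effect.** If loss after month 3 depends only on the 3-month value, the bias in an arm's observed 6-month mean is the regression slope on the 3-month value times the shift in the mean 3-month value among those who stay.

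- Slope for the raw 6-month value: 0.8.
- Slope for change: 0.8 − 0.6 = 0.2.

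Under these correlations, the bias on change is therefore a quarter of that on the raw value (both have SD 1). Results for different loss patterns, logistic in the 3-month value:

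| Loss | Raw 6-month value | Change |
|---|---|---|
| 25% v 5%, slope 1 to 2 per SD | about 0.14 to 0.19 SD | about 0.04 SD |
| 22% v 8%, slope 1 per SD | 0.09 SD | 0.02 SD |
| 15% in each arm, equally selective | about 0 | about 0 |
| 15% in each arm, purely random | about 0 | about 0 |

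At 25% v 5% the type I error of the test on change is about 6%. A likelihood estimate that uses the 3-month value was unbiased within simulation error in all these settings, as expected when loss is explained by observed values.

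**The case against.** The strongest reply is that section 2.14 contains no rule for dropping patients. A t-test can be run on imputed data, and missing-data handling may sit in an analysis plan that is not shown; its absence from an article is no fault. That stands. The point is the method the article does name, and what follows if nothing is imputed.

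A reader might also infer that the 3-month scans are discarded. They are not: they would serve a 3-month comparison and go unused only in an unimputed 6-month test.

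A reader might take section 2.11 as evidence of selective loss in one arm, since surgery is indicated when "conservative treatment with the TCM regimen for 3 to 6 months has been ineffective (Japanese Orthopaedic Association scores <16"). That section gives indications for surgery. It does not say that such patients leave follow-up or miss the 6-month scan, its first condition applies once all interventions have ended, and its threshold is a JOA score, whereas the calculations above tie loss to the 3-month value of the outcome itself. It makes outcome-related loss conceivable and no more.

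The arm imbalance behind the bias figures is likewise assumed; section 2.13.3 gives only an overall 15%.

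Finally, the quoted sentence specifies a test for matched data without defining the pairs. A paired test does not compare two independent randomised arms. That is a separate defect; the calculations here take the intended analysis to be an ordinary between-arm t-test.

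**Conclusion.** The point holds as a weakness of the named method, not as a demonstrated error in the result. Its firm part is efficiency: about 80% power for a t-test against about 91% for the repeated-measures model, with ANCOVA at 90%, given the assumed correlations, a 0.5 SD effect and 15% random loss. Most of that gap is baseline adjustment; the 3-month visit adds little when loss is random.

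The claim that selective loss biases the 6-month result is stronger than the documents support. Bias needs loss that is both outcome-related and different between arms. Even at 25% against 5%, it is only about 0.04 SD for change from baseline, the stated primary outcome. The larger 0.14 to 0.19 SD applies to a test on raw 6-month values. What the extra visit adds is protection if such loss occurs. The change is worth making because it is cheap, and confidence is moderate because every size above rests on assumed correlations and loss patterns.

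**What to change.** In section 2.14, replace the t-test for volume and JOA with one mixed model for repeated measures comparing the arms. Outcomes: the 3- and 6-month values. Terms: arm, visit, arm-by-visit, baseline and baseline-by-visit, with unstructured covariance. Include all randomised patients with at least one follow-up value, and report the arm difference at the primary visit. Add one sensitivity analysis to the missing-at-random assumption, for example by shifting the values assumed for patients who were lost.

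The cost is a paragraph of text and slightly more analysis work. The model relies on loss being explained by observed values, which is a weaker assumption than the one an unimputed t-test makes.
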